| The SHINE study is a randomized controlled study of the effect of a park-based family support group on multiple outcomes (including stress and physical activity) in a low income population.   1. Primary hypothesis:   Children and caregivers enrolled in the SHINE program will have improved stress compared to those who are not enrolled in the SHINE program.   1. Secondary hypotheses:   Children and caregivers enrolled in the SHINE program will have improved social support, family functioning, physical activity, park visitation, and nature affinity compared to caregivers not enrolled in the program.  Children with obesity, ADHD, and asthma who participate in the SHINE program will show improvements in their symptoms.  The effect of the SHINE intervention will vary depending on the baseline life stressors present in the caregiver or child (the effects of nature interact with baseline stress and are dose dependent) and the dose of nature received.  During a SHINE outing, participants will experience immediate improvements in stress and 30 minutes of moderate-to-vigorous physical activity. | | | | | | | | | |  |
| **Purpose of the study:** What are the specific scientific aims of this study? | | | | | | | | | |  |
| Aim1: To determine changes in stress, social support, family function, physical activity, park visitation, and nature affinity amongst primary care patients ages 4 and older, and their caregivers enrolled in the SHINE intervention compared to those in a control group.Aim 2: To determine changes in BMI, ADHD symptoms, and asthma control for patients enrolled in the SHINE program compared to those who are not.Aim 3: To assess immediate changes in stress and minutes spent in moderate-to-vigorous physical activity by enrolled patients and their enrolled parents during SHINE outings. | | | | | | | | | |  |

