| To evaluate specific aims 1 and 2, the study design uses a randomized controlled trial design.  Potential participants will be given a short description of the study (Please see attached waiver to screen patients). If they agree to be screened, they will be screened for eligibility using a short screening tool.  If they are eligible based on the screening tool, they will consented and enrolled. All enrolled participants (which includes a caregiver and a child per family), will receive:   - Resources to find local parks - A recommendation to be physically active three times a week - A pedometer with a diary to record their daily steps - Three tubes for salivary cortisol collections   They will be asked to:   - Complete a questionnaire - Collect a first morning salivary cortisol during the first week, fourth week, and twelfth week of participation - Return to clinic to complete a questionnaire, and to have their child’s BMI measured, on the fourth week and twelfth week of participation - Turn in their physical activity logs on the fourth and twelfth week visits   Upon completing the baseline measures, participants will be randomized to one of two treatment groups ('A' or 'B') by a computer program (we will use Redcap) and the result recorded. Randomization will be blocked (using random permuted blocks) to ensure that the groups are balanced periodically.  The control group will have no added activities.  The intervention group will be asked to return to clinic on the first, second, and third week of the study at 1 pm - 4pm on Saturday. During these visits, they will meet with clinic staff as well as with other participating families. They will turn in their physical activity logs for a week. They will then board a school bus and travel to one of three local parks (Week 1 = Crab Cove, Week 2 = Temescal Lake, Week 3= Redwood Regional Park). Once at park, they will experience:   1. A warm welcome and ice breaker games 2. 30 minutes of lunch and unstructured play 3. 60 minutes of light walking   They will journal about their outdoor experiences. The journal will include questions about stress and well-being.  The intervention group will also be encouraged to visit a park or be physically active at least three times a week every week for six weeksand will be able to chronicle their outdoor physical activity in their journal.  To assess Aim 3 we will survey only the families in the intervention arm:  During the third SHINE outings, enrolled guardians and children will be invited to wear an accelerometer for the duration of the event. Accelerometers will be programmed to record data in 15-second intervals and will allow us to calculate minutes spent in moderate to vigorous physical activity. Participants will return their accelerometers prior to boarding the shuttles to return home. | | | | | | | | | |  |

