| Table 1 presents a timeline of when data will be collected. The experimental group and control group will follow the same timeline.  1. A questionnaire will be administered at baseline, four weeks, and twelve weeks. The survey questions are detailed in the following question. The survey administers will be blinded to randomized assignment.  2. A saliva sample will be obtained at baseline, four weeks, and twelve weeks. Patients will be given a 1.5 ml tube and asked to gather early morning saliva. This sample will be gathered by the research staff on the day of their follow up appointments, who will then store the sample in a freezer at CHORI until it is sent for cortisol level.  3. All participants will be given a pedometer and a daily log of their steps. They will self-record the number of steps they take each day.  4. During the third SHINE outings, participating caregivers and patients will be invited to wear an accelerometer for the duration of the event. Accelerometers will be programmed to record data in 15-second intervals and will allow us to calculate minutes spent in moderate to vigorous physical activity. Participants will return their accelerometers prior to boarding the shuttles to return home. Families will also receive a journal, in which they will be asked to record their stress before and after the outing.  5. Weight and height will be completed using the measuring tools available at the Primary Care Clinic. | | | | | | | | | |  |
| 1. **Surveys, questionnaires, or psychological tests:**  If applicable, please describe the provisions for administering these measures, the mode of administration, the setting, and if special training or qualifications are necessary. N/A | | | | | | | | | |  |

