| Parental and child stress | Salivary cortisol | Participants will bring in early am cortisol | Baseline, 1 month, 3 months |
| Family Cohesion | FACES IV (Olson, 2011) | 7 item balanced cohesion scale taken by parents | Baseline, 1 month, 3 months |
| Connection to Nature | (Adults) Love and Care for Nature (Perkins, 2010) | 15 item self-report scale used to measure emotional connection to nature, tested for people 18 and older | Baseline, 1 month, 3 months |
|  | (Children) Connection to Nature Index (Bragg et al., 2013) | 16 item scale developed and tested for children aged 8-12 | Baseline, 1 month, 3 months |
| Physical Activity | Pedometry | Journals for use at home | Daily record for 6 weeks by participants in intervention arm |
|  | Accelerometry | Armbands placed during park outings | Week 3 outing |
| Increased Park Usage | One week recall self-report |  | Baseline, 1 month, 3 months |
| Obesity | BMI | Take their weight and height | Baseline, 1 month, 3 months |

Figure 1. Parent predictor and outcome variables

[figure not shown]

Figure 2. Child predictor and outcome variables

[figure not shown]

Supplement: S3 File — (DOCX) [file pone.0192921.s003.docx]

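### Table 1 assigns six weeks of step recording to the intervention arm only, contradicting the procedures that have both arms keep step logs for the Aim 1 comparison of physical activity

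*Protocol*

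**What the plan says.** Table 1 lists pedometry under physical activity, recorded in journals at home, with the timing "Daily record for 6 weeks by participants in intervention arm".

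Three other parts of the protocol describe step recording differently:

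- **Study Design.** The list of what all enrolled participants receive, set out before randomization is described, includes "A pedometer with a diary to record their daily steps". The matching list of what they are all asked to do includes "Turn in their physical activity logs on the fourth and twelfth week visits". For the intervention group's Saturday visits in weeks 1, 2 and 3 the section adds "They will turn in their physical activity logs for a week".
- **Methodology and Data Collection.** Item 3 says "All participants will be given a pedometer and a daily log of their steps" and has participants note their own daily counts. The paragraph that introduces Table 1 as the data-collection timeline says "The experimental group and control group will follow the same timeline".
- **Payment for Participation.** Every participating caregiver and every participating child is given a pedometer.

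On the use of the data, Aim 1 under Purpose of the study is "To determine changes in stress, social support, family function, physical activity, park visitation, and nature affinity" among patients and caregivers "enrolled in the SHINE intervention compared to those in a control group". The secondary hypotheses make the same between-arm comparison. The section on surveys and questionnaires says that activity is measured by self-reported pedometer readings, and also by accelerometry at one of the park outings.

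**The concern.** Table 1 is what a coordinator would use to decide what to collect, from whom and when. Its pedometry row names one arm, and so contradicts the sentence that presents the table as common to both arms. A between-arm comparison of physical activity needs a measure recorded in both arms over the same period. Steps that controls never record cannot be recovered by any later analysis, so this has to be settled in the protocol before data collection.

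The recording period is a second conflict. Table 1 stops at six weeks, while the Study Design section has logs returned as late as week 12. Even with both arms recording, a comparison over unmatched weeks would mix an effect of the programme with an effect of calendar time and of falling diary compliance.

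**Working it through.** No sample-size or power figure is involved, so the check sets the statements side by side.

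**1. Who records steps**

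| Place in protocol | Intervention | Control |
| --- | --- | --- |
| Table 1, pedometry row | yes | not included |
| Study Design | yes | yes |
| Methodology and Data Collection, item 3 | yes | yes |
| Payment for Participation (pedometer issued) | yes | yes |

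The table cell is intact and names the arm, so this is not an artefact of text extraction.

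**2. For how long**

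- Table 1: 6 weeks.
- Study Design: logs returned at the week 4 and week 12 visits. If recording runs to the last return, that is 12 weeks, and 12 − 6 = 6 weeks lie outside the Table 1 window.

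**3. What else could give control-arm activity data**

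- Accelerometry is worn at the third outing. The Study Design section ties it to Aim 3 and to intervention families only, so it gives no control data.
- The one-week recall row in Table 1 concerns park usage, not activity.
- No other activity measure is described in the shown text. The caregiver and child surveys and the activity journal are listed as attachments but are not shown, and neither are Figures 1 and 2.

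**4. What each reading implies for the Aim 1 activity comparison**

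- Under Table 1, control families contributing steps = 0. The difference in mean daily steps between arms cannot be estimated, and only a description of the intervention arm remains.
- Under the procedures, both arms contribute and the difference can be estimated.
- The protocol states no allocation ratio. Assuming 1:1, the control families concerned number 100 / 2 = 50 (the number needed) or 120 / 2 = 60 (the number to be enrolled).

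**5. How logs are handed in under the procedures**

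- Intervention: weeks 1, 2, 3, 4 and 12, up to 5 occasions.
- Control: weeks 4 and 12, 2 occasions.

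These are counts of hand-ins. They show that collection differs by arm, but they do not measure bias or missing data.

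**The case against.** The strongest reply is that one table cell stands against several consistent operational statements. Everyone is issued a pedometer and log, everyone is asked to return logs at two common visits, and both caregiver and child are trained in pedometer and journal use at enrolment. The cell may simply carry over the six-week journal that the Study Design section describes for the intervention group. This stands as far as it goes: it makes the procedures the likelier intention. It does not remove the conflict, because the row is labelled pedometry and no other row covers control steps.

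A reader might infer three stronger conclusions that the documents do not support:

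- **The activity outcome is lost.** That follows only if Table 1 overrides the procedures, and most of the text points the other way.
- **Pedometry is the only activity measure controls have.** The surveys are not shown and may contain an activity item. Table 1 is also not a full list of outcomes: it has no row for social support, ADHD symptoms or asthma control, although the aims name all three. The supportable statement is limited to what the shown text describes.
- **Extra hand-ins in one arm bias the step counts.** This is plausible for self-recorded data, but nothing in the protocol gives its size or direction. It is a reason to report completeness by arm, and no more.

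It may also be said that the analysis weeks belong in a statistical analysis plan. That is fair for the averaging rule, but who records and for how long is fixed by the protocol, which states it two ways.

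**Conclusion.** The contradiction is real and should be corrected. Table 1 conflicts with the Study Design and Methodology and Data Collection sections on which arm records steps and over what period, and with its own introductory sentence on the arms sharing a timeline.

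The consequence is conditional. If the table were followed, the between-arm comparison of physical activity in Aim 1 would have no control data from the only suitable measure described in the shown text. If the procedures were followed, the comparison is available, with a recording window still to be settled.

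The reach is limited. Physical activity is a secondary hypothesis, and the primary comparison of caregiver stress on the PSS does not depend on it. The conclusion rests on the shown text alone and on no numerical assumption; the figure of 50 to 60 control families assumes equal allocation.

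**What to change.** 1. Amend the timing cell of the pedometry row in Table 1 to daily step recording by all participants in both arms.
2. State one recording window and use it in Table 1, Study Design, and Methodology and Data Collection. The investigator has to choose between the six weeks in Table 1 and recording through the week 12 visit. If six weeks is kept, say what the log returned at week 12 is meant to contain.
3. Specify that mean daily steps are compared between arms over the same study weeks, using all logs that cover those weeks regardless of when they were handed in.
4. Report log completeness by arm, such as the proportion of days with a recorded count, because intervention families also hand in logs at the outings.

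Two apparent remedies for the unequal hand-in should be avoided. Reminders to controls in weeks 1 to 3 would add contact to an arm that is meant to receive no extra activity, and could themselves change step counts. Restricting the analysis to logs handed in at weeks 4 and 12 would discard the intervention logs surrendered at the three outings. If each covers one week, that is up to 3 of the 6 weeks in the Table 1 window.

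The cost is one table cell, matching wording in two sections, and two sentences on analysis and reporting. Controls are already due to receive the pedometer and log, so no new equipment or visit is needed. If the longer window is chosen, recording and data entry extend accordingly.

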| Surveys will be administered in-person and at clinic. The adult questionnaire will take 20-30 minutes of time. The child questionnaire will take 10 minutes, and can be administered simultaneously to the adult questionnaire. We will use tablets to administer the questionnaire, with paper versions available to those who would prefer to fill the survey themselves on a paper version.  Special training or qualifications are not necessary to administer these tests. However, as several of the questions include sensitive topics, a clear protocol is in place for dealing with potential issues that may come up. The population serves by the UCSF Benioff Children’s Hospital Oakland experiences high levels of stress related to poverty. For that reason, we anticipate that a significant portion of respondents will have high stress scores. We will also be asking about social isolation and loneliness. We anticipate that a proportion of respondents will answer that they feel socially isolated. We will also be asking about childhood adversity, which includes questions about domestic violence, community violence, and abuse in the home. We anticipate that the proportion answering that these adverse events have happened to the enrolled child will mirror, at least, national averages of 8% of respondents for each of these questions (Child and Adolescent Health Measurement Initiative, 2013, available at; [www.childhealthdata.org](http://www.childhealthdata.org)).  In order to properly support families who disclose sensitive issues, we will enact a very clear protocol. For families with high stress, social isolation, or potentially reportable conditions, the principal investigator will always be contacted. The principal investigator will screen the family for safety. The principal investigator [name], is currently an attending pediatrician in the adolescent medicine and homeless clinics. She has experience enacting safety screens and mandatory reporting protocols through her experiences in these clinics.  All families who reveal stress, loneliness, or adversity, will be given mental health resources. If the patients additionally screen positive for a reportable condition, or if there is concern for their current safety, the principal investigator will contact the on-call social worker. The social worker at the Primary Care Clinic will then work with the principal investigator to enact mandatory reporting. If the social worker is not available, the principal investigator will contact the hospital’s social work office to find back up social work support.This protocol is the same protocol used by all mandatory reporters, including clinicians in the primary care clinic.  Physical Activity will be measured through self-report of pedometer readings. The parent will be responsible for recording the number of steps walked daily in their own journal. The caregiver will be responsible to helping children enter their number of steps in the child’s own journal. If the child is old enough to enter their own steps, that is acceptable. Both the caregiver and the child will be trained to use the pedometer and the journal upon enrollment in the study.  Salivary cortisol will be measured through obtaining early morning saliva samples. Caregivers and children will be expected to submit saliva samples. They will be trained to do so by the research assistant during study enrollment, and will have a phone number to call in case they have any questions.  Physical activity will also be measured through accelerometry. Research staff will place and remove accelerometers for enrolled caregivers and children during one of the park outings. | | | | | | | | | |  |

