| Despite mounting evidence that nature matters for human health, we are not aware of any prospective intervention trials looking at the use of nature as a health intervention. Like other protective factors, such as the presence of a caring adult, safe play places, greater stimulation, the presence of green-space in a child’s life has been empirically linked to greater resilience. Nature has been proposed as a buffer to stress through several pathways: by providing a space for friends and families to gather (thereby increasing social support and improving family relationships), by increasing opportunities for physical activity, and by improving cognition. Research to date suggests that participation in outdoor activities facilitates a sense of connectedness to place. This sense of attachment, we postulate, may also provide a form of social support. Families served by Children’s Hospital Oakland Primary Care Clinic experience high levels of stress. As a safety-net clinic, the primary care clinic serves a diverse set of patients, with a common thread of poverty. The Stay Healthy In Nature program was developed to encourage stress management skills through play and physical activity in parks. It was formed through a collaboration between health care providers at Children’s Hospital Oakland Primary Care Clinic and the staff at East Bay Regional Parks District (EBRPD). This six week program uses a combination of facilitated and independent outings into local parks to encourage sustained behavior change and measurable health benefits. The SHINE study is a randomized controlled study of the effect of this park-based family support group on multiple outcomes (including stress and physical activity) in a low income population. The study is supporting by EBRPD and the National Regional Parks and Association, and will take place during summer and fall 2015. |

| Table 1. Outcome variable, measurement tool, and timing | | | |
| --- | --- | --- | --- |
| Outcome variable | measurement tool | short description | timing |
| Parental Stress | PSS-10 (Lee, 2012) | 10 item scale used to measure one's self-report of stress. Reliability and validity scores have been performed for adults | Baseline, 1 month, 3 months |
| Child Stress | PSQ 8-11 | 19 item self-report. 9 items measure psychological stress, while 10 items measure physiological stress | Baseline, 1 month, 3 months |

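### Table 1 schedules pedometry for six weeks in the intervention arm only, contradicting the protocol text; if Table 1 is followed, physical activity cannot be compared between arms at 3 months or at any other time

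*Protocol*

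**What the plan says.** Aim 1 (Purpose of the study) lists physical activity among the outcomes to be compared between SHINE families and controls. The section on surveys and questionnaires names the measure: "Physical Activity will be measured through self-report of pedometer readings".

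Three places describe when and by whom steps are recorded.

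- **Study Design, additional description.** The items given to all enrolled participants include "A pedometer with a diary to record their daily steps". The same participants are asked to "Turn in their physical activity logs on the fourth and twelfth week visits".
- **Methodology and Data Collection.** "All participants will be given a pedometer and a daily log of their steps", and "They will self-record the number of steps they take each day". No end date is given. The section points to Table 1 as the data-collection timeline and adds: "The experimental group and control group will follow the same timeline".
- **Table 1, Physical Activity, Pedometry row.** "Daily record for 6 weeks by participants in intervention arm".

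The only other physical activity row in Table 1 is accelerometry, at the week 3 outing. The rows for stress, cortisol, family cohesion, connection to nature, park use and BMI are all scheduled at baseline, 1 month and 3 months.

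**The concern.** The Table 1 cell differs from the text in two ways: how long steps are recorded, and in which arm. The three passages cannot all be followed. The text itself cites Table 1 as the timeline, so staff who prepare log pages or data-entry forms could reasonably work from it.

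At stake is a named between-arm outcome. Steps not written down during follow-up cannot be recovered, and no later analysis plan can supply them. Restoring the control arm alone would still leave no 3-month value. Extending the window alone would still leave no comparator.

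**Working it through.** The protocol states no figure that depends on this schedule, so there is nothing of its own to reproduce. The check is to compare the passages and count weeks.

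**Inputs**
- Follow-up: 12 weeks (Duration of Subjects' Participation), that is 12 × 7 = 84 days.
- Pedometry under Table 1: 6 weeks, that is 6 × 7 = 42 days, intervention arm only. No start week is given.
- Log hand-in: weeks 4 and 12, all participants (Study Design).
- Accelerometry: one outing, week 3, intervention arm only (Study Design; Table 1).

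**Step 1. When does a six-week record end?** A record that starts in week s ends in week s + 5.
- s = 1: ends in week 6; weeks 7–12 have no steps (12 − 6 = 6 weeks).
- s = 4, after the three outings: ends in week 9; weeks 10–12 have no steps (12 − 9 = 3 weeks).
- To reach week 12, s would have to be 12 − 5 = 7. Nothing in the protocol describes a start that late.

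**Step 2. What exists under each reading?**

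| | Table 1 governs | Text governs |
|---|---|---|
| Intervention arm, days scheduled | 42 of 84 (50%) | daily, no stated end; logs collected at week 12 |
| Control arm, days scheduled | 0 of 84 | same as intervention arm |
| Week-12 step value | none in either arm | both arms |
| Week-4 between-arm comparison | not possible (no controls) | possible |
| Week-12 between-arm comparison | not possible | possible |

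**Step 3. Does another measure fill the gap?** Accelerometry is worn during a single supervised outing that controls do not attend, so it gives neither a comparison nor a late value. Park use is recalled at 3 months, but Table 1 treats it as a separate outcome.

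**The case against.** The strongest reply is that the text already provides what Table 1 leaves out. Two sections give pedometers and logs to everyone, one sets a common timeline, and a week-12 hand-in is specified. On that reading Table 1 holds a careless entry, perhaps describing the six weeks in which intervention families may chronicle outdoor activity in a journal, and step data to week 12 exist in both arms. This stands in part: the protocol has not settled that the data will be absent. It does not remove the conflict, because the row is labelled pedometry and the text names the table as the schedule.

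Several stronger readings are tempting but not supported.

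- A reader might infer that recording stops at the same moment as the encouragement to be active. Both last six weeks, but neither has a stated start. All participants also receive a recommendation to be active three times a week that has no end date.
- A reader might infer that the trial sets out to test lasting change in activity. The Study Abstract says the program uses park outings "to encourage sustained behavior change and measurable health benefits". That describes the program's purpose. The hypotheses and aims name physical activity without a durability claim.
- A reader might try to quantify how far a six-week step average overstates the 3-month effect. That needs six weeks of steps in both arms, which no passage describes.

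Two limits also apply. Physical activity is a secondary outcome. The activity journal and the surveys are attachments that are not shown, so other activity items in them can be neither confirmed nor excluded; Table 1 lists none.

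**Conclusion.** The protocol contradicts itself on the duration of step recording and on the arm. The consequence is conditional. If Table 1 governs, the Aim 1 comparison of physical activity cannot be made at 1 month, 3 months or any other time, because controls have no step data. The intervention arm alone would also have no week-12 value for a start in week 1 or week 4. If the text governs, the comparison can be made at both visits.

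The conclusion assumes that the final visit is at week 12, as in Study Design and Methodology and Data Collection, and that no unseen attachment carries a substitute measure. It does not depend on the exact start of the six weeks, provided they start before week 7. The primary stress outcome is unaffected. The correction should still be made, because it is small and the loss it prevents is permanent.

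**What to change.** Change the pedometry timing in Table 1 to agree with Study Design and with Methodology and Data Collection: daily step logs by caregivers and children in both arms through the week-12 visit. If that burden is judged too great, require at least the 7 days before the week-4 visit and the 7 days before the week-12 visit, in both arms, and amend the text to match.

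State that physical activity is compared between arms as mean daily steps at 1 month and 3 months. Any mean over weeks 1–6 should be kept as a separate in-programme measure.

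The cost is one table cell and additional log pages. Pedometers are already issued to every caregiver and child, and the week-12 hand-in is already planned. The downside is some extra diary burden and probably more missing log days late in follow-up.
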